Aim: To explore the safety, tolerability, and initial efficacy of psilocybin administered with psychological support compared to Treatment as Usual (TAU) in adolescents and young adults aged 16-35 with anorexia nervosa (AN).

Primary Objective: To assess the safety and tolerability of psilocybin 25 mg in this population.

Secondary Objectives: To evaluate the efficacy of psilocybin with psychological support in reducing AN symptom compared to TAU, investigate potential mechanisms of action through self-report questionnaires, neuroimaging and BDNF analysis, and conduct qualitative analysis of subjective experiences.

Trial Design: Open, randomized controlled trial with two arms: (1) two doses of psilocybin (25 mg) with psychological support with one month apart and alongside treatment as usual, and (2) Treatment as Usual (TAU).

Trial Population: Adolescents and young adults aged 16-35 diagnosed with anorexia nervosa.

Number of Subjects: 40 participants (20 per group).

Inclusion Criteria: Diagnosed with AN per DSM-5, aged 16-35, BMI >16, who have experienced at least one period of weight gain followed by weight loss.

Exclusion Criteria: Psychosis, bipolar disorder, substance use disorder, contraindicated medications, severe medical conditions, or metal contraindications for MRI.

Intervention: Two doses of 25 mg psilocybin with psychological support, or TAU. Psilocybin sessions will be accompanied by preparatory and integration sessions.

Investigational Medicinal Product Dosage Administration: Psilocybin 25 mg administered orally during supervised sessions.

Ethical Considerations/Benefit-Risk: Comprehensive safety monitoring, support during sessions, and procedures in place for managing any adverse events. First 25 participants included above 18 years of age, followed by 15 patients between 16-17 years of age. Safety review committee after first 10 psilocybin dosing sessions to review adverse events and protocol adherence. Literature on psilocybin clinical trials report low risk for adverse events and large gap in treatment options for patients with relapse in anorexia nervosa.

Planned Duration of the Trial: Q3 2025 – Q2 2027.

2. Background and Rationale

This pilot study will assess the safety, tolerability, and preliminary efficacy of administering 25 mg of psilocybin, spaced one month apart, in combination with treatment as usual (TAU) for adolescents and young adults aged 16-35 with AN. The study will compare this combined approach to the effects of TAU alone. Additionally, it will explore potential mechanisms of action through self-reports, neurobiological assessments, and neuroimaging techniques.

**Anorexia Nervosa**

AN impact approximately 1.0% of older female adolescents and young women. This heterogeneous psychiatric disorder is characterized by significantly low body weight, distorted body image, and an intense fear of weight gain (Hoek, 2006). More than half of adult patients with AN develop a chronic and severe form of the condition (Fichter et al., 2017; Steinhausen, 2002).

AN is known for having the highest mortality rate among psychiatric disorders, being approximately 5 times higher than that of the general population (Arcelus et al., 2011). It also leads to a substantial decline in health-related quality of life (Dejong et al., 2016). Anorexia nervosa (AN) affects multiple organ systems due to severe weight loss and malnutrition, impacting the cardiovascular, gastrointestinal, hematological, and endocrine systems (Westmoreland et al. 2016). Amenorrhea, resulting from disruptions in the hypothalamic-pituitary-gonadal axis, is common, leading to infertility (Puckett et. al. 2021). Low BMI and decreased gonadal function are suggested as key predictors of osteoporosis and fractures in patients with AN (Steinman & Shibli-Rahhal, 2019). In one study, 54% of patients had osteopenia and 21% had osteoporosis in the lumbar spine within 3-4 years of diagnosis ([Zipfel](https://www.researchgate.net/profile/Stephan-Zipfel?_tp=eyJjb250ZXh0Ijp7ImZpcnN0UGFnZSI6InB1YmxpY2F0aW9uIiwicGFnZSI6InB1YmxpY2F0aW9uIn19) et al., 2002).

The age of onset for AN typically shows a bimodal distribution, peaking at 14 and 18 years of age (Halmi et al., 1979). Research indicates various psychological factors, including difficulties with affect regulation, dichotomous thinking, mental rigidity, and a limited capacity for mentalization, might contribute to the persistence of severe chronic AN (Halmi, 2013).

Different psychotherapies have shown to be somewhat effective in the treatment of AN, one review including 5590 patients showed 46% recovered AN patient within 4 years, however 20% remained chronically ill (Steinhausen, 2002). Earlier treatment was associated with better chances of recovery. However, in those who recover, the relapse rate can be more than 50% (Khalsa, 2017).

**Psilocybin and psychedelic therapy**

Psilocybin is part of a group of hallucinogenic compounds, primarily acting as agonists of the 5-hydroxytryptamine (5-HT) 2A receptor, induce effects in domains of cognition, emotion, perception and self-awareness (Swanson, 2018). Although limited in size, clinical trials including various psychiatric disorders indicate the potential beneficial effects of psychedelic based interventions, especially with psilocybin (Carhart-Harris and Goodwin, 2017).

Personality changes have been found to persist up to at least one year after a single high dose (30 mg/70kg) of psilocybin (MacLean et al., 2013). Similarly, change in the personality trait after intake of another psychedelic substance, Lysergic-acid-diethylamide (LSD), intake has been linked to increased variability and complexity in brain activity (Lebedev et al., 2016). Although, the therapeutic mechanisms are still mostly unknown (Mertens et al., 2021).

While research on psychedelics is growing, studies focusing on the use, experiences, and effects of these substances among adolescents and young adults remain limited (Bates and Trujillo, 2021). There's an acknowledged need for novel psychiatric treatments for adolescents, like adults, but with additional considerations for developmental stages and informed consent processes (Rajwani, 2022).

**Psychedelics and eating disorders**

Ayahuasca is a psychoactive brew typically consisting of plants containing dimethyltryptamine (DMT), a classic psychedelic substance like psilocybin, inducing altered states of consciousness during ceremonial use. Two qualitative studies involving a total of 29 participants who underwent ayahuasca ceremonies for eating disorders (ED) have been published (Lafrance et al., 2017; Renelli et al., 2020). The studies identified five key themes from the participants' experiences: (1) effectiveness of ayahuasca in reducing AN symptom and aiding overall recovery, (2) deeper awareness of the root causes of ED, (3) processing of intense emotions and memories, (4) insights into love, self-love, and self-care, and (5) a spiritual aspect to their healing and recovery.

Recent reviews suggest mechanisms of change for psychedelics in AN patients, such as increased serotonin system signaling and enhanced cognitive flexibility (Calder et al., 2023; Foldi et al., 2020). The ability of psychedelics to foster cognitive flexibility, a well-documented phenomenon, is considered a key factor in therapeutic processes (Davis et al., 2020; Lebedev et al., 2016; Carhart-Harris et al., 2016b). This is particularly relevant for AN patients, who often exhibit rigid thinking and behavior, a factor contributing to treatment resistance and the development of severe, persistent symptoms (Halmi, 2013). In addition, psilocybin and other classical psychedelics can induce temporary ego-dissolution, potentially offering new perspectives on self-image (Nour et al., 2016; Mason et al., 2020).

Currently, there are no approved pharmacological treatments for anorexia nervosa (Rahkonen et al., 2022). However, three pilot clinical trials have been approved and activated. NCT04052568 from John Hopkins is currently active. NCT04505189 from Imperial College is finished but not published. The third pilot study assessed the clinical tolerance and safety of 25mg psilocybin supported by psychological intervention in female AN patients with a BMI of 19 (Peck et al., 2023). The study found no significant changes in ECG, vital signs, or suicidality, and all adverse events (AEs) were mild and temporary. Two participants developed asymptomatic hypoglycemia post-treatment, which resolved within 24 hours with no other significant changes in laboratory values. Most participants reported subjectively meaningful experience, and a majority expressed that a second dose would have been beneficial. The study also observed significant reductions in eating disorder symptoms one-month post-treatment.

**Functional magnetic resonance imaging (fMRI) and psilocybin**

In a psilocybin fMRI study (Carhart-Harris et al., 2012), 30 volunteers underwent arterial spin labeling and BOLD fMRI assessments to observe the transition from a normal to a psychedelic state. The study revealed a noteworthy decrease in cerebral blood flow and BOLD signals, particularly in key brain regions such as the thalamus, anterior and posterior cingulate cortex. A significant finding was the reduced activity in the ACC/medial prefrontal cortex, correlating with the intensity of subjective psychedelic experiences.

In another study comparing psilocybin and escitalopram for major depressive disorder (Daws et al., 2022), psilocybin produced a rapid and lasting antidepressant response, linked to changes in brain network modularity measured by fMRI. This contrasted with the less pronounced antidepressant effect of escitalopram, which showed no significant changes in brain network organization.

In a recent longitudinal study comparing psilocybin and methylphenidate (Siegel et al., 2023, preprint), psilocybin showed a greater disruption in brain connectivity, particularly in the default mode network, involving desynchronization across spatial scales. Additionally, psilocybin induced a persistent decrease in functional connectivity between the anterior hippocampus and cortical regions related to the default mode network, with normalization observed after six months.

In summary, these studies collectively demonstrate that psilocybin induces profound alterations in brain function and connectivity. These alterations include decreased cerebral blood flow and activity in specific brain regions, changes in brain network organization, and disruptions in connectivity across various brain networks. These findings provide a deeper understanding of the neurobiological mechanisms underpinning the effects of psilocybin, with potential implications for its therapeutic use. However, research on the long-term effects of psychedelic compounds on neural processing is still limited and needs to be investigated further, specifically in relation to treatment effects in clinical trials (Wall et al., 2023).

**fMRI and AN**

Research on AN has produced a variety of findings regarding brain activation in patients (Fugleset et al., 2016). Studies highlight altered activation in fronto-striato and limbic circuits, pivotal in AN 's pathophysiology. Many studies have focused on limbic dysfunction, and its impact on emotional and perceptual neural circuits, using neural activation in relation to food cues, and body image distortion (i.e. disorder relevant stimulation protocols) as a model to investigate these issues (Bronleigh et al., 2022). These studies collectively indicate altered neural activity across multiple brain regions (frontal, parietal, temporal, occipital lobes, amygdala, striatum, thalamus, cerebellum), potentially contributing to various AN symptoms and behaviors.

One aspect of interest is how anxiety and pathological fear learning might lead to conditioned neural responses to food stimuli, potentially explaining the phobic avoidance of food in acute AN cases (Kaye et al., 2009). Limbic information processing in AN might be inhibited by cognitive areas like the dorsolateral prefrontal cortex and parietal cortex, possibly contributing to restrictive eating behaviors. While results from fMRI studies are diverse, they align interestingly with theories of neurocircuit dysfunctions in AN.

There's also evidence suggesting that increased activations in fronto-striatal circuits are linked to the maintenance of restrictive eating habits in AN (Steward et al., 2018). Functional network connectivity studies, though varied, generally indicate disrupted connectivity in executive networks, the default-mode network, and the salience network across eating disorders.

***Rationale for fMRI in a study of a psilocybin intervention for AN***

Functional MRI allows for the detailed observation of brain activity and connectivity changes as a function of treatment. Given that fMRI studies on psilocybin have revealed significant alterations in brain networks, particularly in regions associated with mood regulation and cognitive processing, it can provide critical insights into how psilocybin affects the brain regions implicated in AN. Moreover, fMRI has already demonstrated its utility in identifying altered neural activity in AN, particularly in circuits related to food perception, emotional processing, and body image. By using fMRI to track changes in these specific brain regions before and after psilocybin treatment, we can gain a deeper understanding of the neurobiological impact of psilocybin on AN and potentially identify biomarkers for treatment efficacy and optimization.

**Potential impact on synaptic plasticity**

Brain-Derived Neurotrophic Factor (BDNF) is a protein that plays a crucial role in neuroplasticity (Lohof et al., 1993; Cohen-Cory et al., 2010). Animal studies have shown that psilocybin promotes neurogenesis and synaptic plasticity (Moliner et al., 2023; Ly et al., 2018). It is indicated that 5-HT2A agonists increase cortical BDNF expression and BDNF protein levels in rodent brain neurons. Notably, individuals with AN exhibit reduced serum BDNF levels (Nakazato, 2003). However, the potential impact of psilocybin on BDNF levels in patients with AN remains unexplored. Investigating the relation between BDNF change before and after a two-dose psilocybin treatment in patients with AN could shed light on the neurobiological mechanisms of psilocybin’s action in the AN population and potentially provide valuable insight for treatment efficacy and optimisation.

3. Benefit-Risk Evaluation

Benefits:

Psilocybin, a naturally occurring psychedelic compound, has shown significant potential as a novel therapeutic intervention for various psychiatric conditions, particularly those characterized by treatment resistance and chronicity. Evidence from clinical trials has demonstrated significant antidepressant effects of psilocybin in populations with major depressive disorder (MDD) and treatment-resistant depression (TRD). In these trials, psilocybin has been associated with rapid and sustained reductions in depressive symptoms, with effects lasting weeks to months after a single or limited number of dosing sessions.

Beyond the reduction in symptoms, participants in these trials have often reported experiencing meaningful and transformative experiences, which they describe as personally insightful and emotionally significant. These self-reported experiences are believed to play a crucial role in the therapeutic effects of psilocybin, potentially leading to enhanced emotional processing, improved mood, and increased cognitive flexibility. These outcomes are particularly relevant for patients with anorexia nervosa (AN), a condition marked by rigid thought patterns, emotional avoidance, and a high degree of treatment resistance.

Currently, the available treatments for AN, including cognitive behavioural therapy (CBT) and pharmacotherapy, often result in limited efficacy and high relapse rates, particularly in cases where the disorder has become chronic. There is a critical need to explore new treatment modalities that can offer more substantial and sustained benefits. Psilocybin-assisted therapy represents a promising new avenue, especially considering its observed effects in enhancing cognitive flexibility and emotional insight, which are core areas of dysfunction in AN. Emerging research suggests that psilocybin-assisted therapy can address these gaps by fostering cognitive flexibility, reducing emotional rigidity, and enhancing the capacity for introspection and insight. This positions psilocybin as a potential new adjunctive intervention in the treatment of AN.

This study targets an age group (16-35 years) where AN often begins to develop into a chronic condition, making early intervention with innovative therapies particularly crucial. Individuals in this age range frequently show entrenched patterns of thought and behaviour that are resistant to standard treatments. By including this demographic, the study aims to evaluate whether psilocybin can disrupt these patterns, offering a potential shift in treatment outcomes that could prevent or mitigate the progression of AN into a more severe, chronic state.

In summary, the potential benefits of this study include:

- Evaluating the antidepressant and transformative effects of psilocybin in a population with few effective treatment options,
- understanding the role of meaningful self-reported experiences in therapeutic outcomes,
- Exploring potential biomarkers, such as BDNF levels and neuroimaging changes, to enhance future personalization of treatments.
- Targeting a critical age range for early intervention in anorexia nervosa.

**Risks and Adverse Events Associated with Psilocybin**

Previous research using doses of 30 and 40 mg reported no serious adverse events (Griffiths et al., 2006, 2011; Bogenschutz et al., 2022).

Key risks of psilocybin, as noted in literature, include prolonged psychotic symptoms, flashback phenomena or Hallucinogen Persisting Perceptual Disorder (HPPD), and anxiety reactions. Studies at the John Hopkins Center for Psychedelic Research, encompassing over 300 participants and 600 dosing sessions with 25mg psilocybin, recorded no cases of HPPD. HPPD itself is rare, with a prevalence of 4-4.5% among lifetime users of hallucinogens, though the specific incidence related to psilocybin is unclear (Kurtom et al., 2019). Prolonged psychotic responses in clinical psilocybin studies are infrequent, less than 1% (Studerus et al., 2011).

Anxiety during psilocybin experiences is common (Griffiths et al., 2006; Carhart-Harris et al., 2016a). A survey involving 1993 participants (mean age 29) exploring challenging experiences with psilocybin found that 84% benefited, despite psychological distress. The severity of the experience positively correlated with long-term increases in well-being (Carbonaro et al., 2016).

This study includes robust preparatory and integration sessions to minimize distress and maximize therapeutic outcomes. Therapists will receive specialized training to handle challenging experiences in real time.

Although the MRI examinations, during which patients need to lie still for about 1 hour, might be perceived as uncomfortable by some, they pose no health risk for the patient if routine safety precautions are followed (i.e. careful screening for contraindications for undergoing MRI and ensuring that no ferromagnetic metal objects are brought near the scanner).

**Suicidality**

A study on psilocybin for depression treatment noted two cases of suicidal behavior in the 25 mg group, compared to two in the 10 mg group and none in the 1 mg group within three weeks post-dosing (Goodwin et al., 2022). Another study comparing 25mg psilocybin with escitalopram for depression found no increase in serious adverse events or suicidal behavior in either group (Carhart-Harris et al., 2021).

This study includes active monitoring for suicidal ideation and behaviour during and after treatment sessions, with immediate intervention plans in place

**Specific clinical AN related risk**

One study of psilocybin 25mg for adults with AN, reported no clinically significant changes in ECG, vital signs, or suicidality levels (Peck et al., 2023). Only two participants experienced asymptomatic hypoglycemia post-treatment, which resolved within 24 hours. Additionally, no significant changes were noted in laboratory values. All adverse events (AEs) observed were mild and temporary. The overall participant feedback indicated that the treatment was generally well-received and deemed acceptable.

To mitigate potential risks, participants in this study will undergo comprehensive medical screening, including blood tests and ECG, before dosing session. A trained physician will be present during all psilocybin sessions to address medical emergencies, if needed.

4. Trial Objectives

For full list of measurements, please see attachments.

4.1 Primary Objective

- To assess the safety and tolerability of psilocybin 25 mg in adolescents and young adults with anorexia nervosa.

4.2 Secondary Objectives

- To evaluate the efficacy of psilocybin with psychological support in reducing AN symptom compared to TAU and time to relapse within 12-month follow-up.

- To investigate potential mechanisms of action through neuroimaging (fMRI), using both resting-state and task-based paradigms for estimation, and biomarker analysis (BDNF levels) with in six-month follow-up.

- To assess changes in mental health, well-being, and personality traits within 12-month follow-up.

- To conduct a qualitative analysis of the subjective experiences of patients, their relatives, and therapists at last follow-up at 12 months.

4.3 Primary Endpoint

- **Safety:** Incidence of adverse events (AEs) and serious adverse events (SAEs) during the trial period.

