**Rationale for Composite Outcome:**
This composite endpoint captures both clinical (BMI, hospitalization) and patient-centered (symptom deterioration) measures, aligning with the study’s aim to evaluate the efficacy of psilocybin in reducing the risk of relapse during a critical recovery period.

- Time to **Response:**

A clinically significant improvement in weight and psychological symptoms during the treatment period.

**Criteria**: **BMI Increase**: ≥10% increase in BMI from baseline (e.g., BMI 16 → BMI 17.6) or reaching a BMI ≥18.5 if achievable within the study period.

- Time to **Remission:**

The achievement and maintenance of weight restoration and psychological well-being, with no significant symptoms of anorexia nervosa.

**Criteria**: **Weight Restoration**: BMI ≥18.5 sustained for at least four weeks, or a weight within 90-95% of ideal body weight adjusted for age and height.

- Changes in AN symptom severity (measured by the Eating Disorder Examination from baseline to primary endpoint and follow-up 6 and 12 months.

- Changes in well-being from baseline to primary endpoint and follow-up 6 and 12 month.

- Changes in personality traits from baseline to primary endpoint and follow-up 6 and 12 months

- Changes in brain resting state connectivity (measured by fMRI), and commonly used task-based fMRI paradigms from baseline to primary endpoint. The task-based paradigms will involve food-related conditions, commonly used in the population (Celeghin et al., 2023; Bronleigh et al., 2022) as well as established paradigms involved in processing reward anticipation (Knutson et al., 2000; Ventorp et al 2022)

- Changes in peripheral BDNF measured in platelet-poor EDTA plasma from baseline to primary endpoint.

5. Trial Design and Procedures

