**5.2 Procedures and Schedule of Assessment**

All procedures will be conducted at the University Hospital for Psychiatry, [name], except the fMRI assessments which are performed at the The National 7T Facility in Lund. All assessments will be carried out by qualified personnel appointed by the principal investigator, including medical doctors, nurses, and psychologists. The National 7T Facility will appoint qualified personnel for fMRI assessment.

The duration of the entire trial is from the first screening of the first patient to the last follow up of the last patient. For each patient participant, the duration of the trial is from the screening to the last follow up at week 52 (12 month).

Patient rehospitalization and additional interventions data are collected in patient journal registers.

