**Primary Endpoint Week 9**

Includes full safety and outcome evaluations:
- fMRI

- blood sampling (including glucose, liver, kidney, glucose, BDNF)
- Vital signs, ECG, U-tox

- BMI
- AE/SAE monitoring
- Readiness and Motivation Questionnaire (RMQ)
- General Change Mechanisms Questionnaire (GCMQ)
- Patient Health Questionnaire (PHQ-9)
- Generalized Anxiety Disorder scale (GAD-7)
- Eating Disorder Examination Questionnaire (EDE-Q)
- Columbia-Suicide Severity Rating Scale (C-SSRS)
- Brief Psychiatric Rating Scale – Extended (BPRS+)
- Satisfaction With Life Scale (SWLS)
- Positive and Negative Affect Schedule (PANAS)
- Harmony in Life Scale (HILS)
- Ten Item Personality Inventory (TIPI)
- Honesty-Humility Scale (HH)

- Visual size estimation (EGON)

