9.3 Reporting and Registration of Adverse Events

- AEs will be recorded by clinicians in the research team at each contact point with a study participant and reported in the REDCap documentation system and a manual standardized AE log template and serious events will be reported to the relevant authorities.

Serious adverse events (SAEs) will be reported within 24 hours of the investigator becoming aware, in accordance with Article 41 of CTR 536/2014.

- Suspected Unexpected Serious Adverse Reactions (SUSARs) will be reported to all investigators and Läkemedelsverket (LVM).

- All AEs and SAEs will be collected from Dosing 1 until final follow-up at 12 months.

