**Monitoring Procedures**

Monitoring will include the following key elements:

- **Qualified Monitors Will Oversee the Study to Verify:**
  - That the rights, well-being, and safety of participants are protected.
  - That all protocol procedures are followed, including adherence to inclusion/exclusion criteria, informed consent, and investigational treatment administration.
  - That all data collected in the electronic Case Report Form (eCRF) is accurate, complete, and verifiable from source documents.
  - That adverse event (AE) reporting follows regulatory guidelines and timelines.
  - Serious adverse events (SAEs) will be reported within 24 hours of the investigator becoming aware, in accordance with Article 41 of CTR 536/2014.
  - That all study personnel maintain GCP compliance and are adequately trained.
- All AEs and SAEs will be collected from first dosing until final follow-up at 12 months.

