**Data Retention and Security Measures**

- All study data will be retained for a minimum of 25 years post-study completion, as required by clinical trial regulations.
- Secure long-term storage will be ensured by Kliniska Studier Forum Söder in compliance with data archiving policies, and access will be restricted to authorized personnel only.
- Upon study closure, the database will be locked to prevent further modifications, and final datasets will be archived in compliance with EMA and national regulatory requirements.

15. Notification of Trial Completion, Reporting, and Publication

The study team aims to present the findings at psychiatry and psychedelic science conferences. Publish in high-impact journals focusing on psychedelics, psychiatry, neurology, and pharmacology. Press releases to major healthcare news outlets and the public. Host webinars, lectures and participate in forums for mental health professionals and researchers in Sweden. Share findings with collaborating academic institutions for further research and teaching. Release follow-up studies and long-term effect analyses.

CTIS will be reported in CTIS within one year after completion of study (six months follow-up of active arm and controls, not including the switch).

16. References

Barrett, F. S., Doss, M. K., Sepeda, N. D., Pekar, J. J., & Griffiths, R. R. (2020). Emotions and brain function are altered up to one month after a single high dose of psilocybin. *Scientific Reports, 10*(1), 2214. <https://doi.org/10.1038/s41598-020-59282-y>

Bates, M. L. S., & Trujillo, K. A. (2021). Use and abuse of dissociative and psychedelic drugs in adolescence. *Pharmacology Biochemistry and Behavior, 203*, 173129. https://doi.org/10.1016/j.pbb.2021.173129

Bogenschutz, M. P., Ross, S., Bhatt, S., et al. (2022). Percentage of heavy drinking days following psilocybin-assisted psychotherapy vs placebo in the treatment of adult patients with alcohol use disorder: A randomized clinical trial. *JAMA Psychiatry, 79*(10), 953–962. https://doi.org/10.1001/jamapsychiatry.2022.2096

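### The primary AE/SAE endpoint has inconsistent time frames, and its literal 12-month window runs past the control switch and starts at a dosing that TAU does not have

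*Protocol*

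**What the plan says.** Three time frames appear in the current protocol text.

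- **12 months.** Section 4.3 sets the primary endpoint as "Incidence of adverse events (AEs) and serious adverse events (SAEs) during the trial period". Section 5.2 says: "For each patient participant, the duration of the trial is from the screening to the last follow up at week 52 (12 month". Section 9.3 says: "All AEs and SAEs will be collected from Dosing 1 until final follow-up at 12 months", and section 11.2 (Monitoring Procedures) repeats this. Section 5.4 ends the trial at the last participant's week-52 visit.
- **Week 9.** Section 5.2 titles a visit "Primary Endpoint Week 9" and lists AE/SAE monitoring among its assessments. Section 4.4 uses the term as a time point, for example "Changes in well-being from baseline to primary endpoint and follow-up 6 and 12 month". Section 8.2 schedules laboratory tests by the same label.
- **Six months.** Section 15 times the CTIS report from "completion of study (six months follow-up of active arm and controls, not including the switch".

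Section 10.2 plans a between-group comparison of the number of participants with AE/SAE (chi-squared or Fisher, with RR or OR and confidence intervals) and states no cut-off. Section 7.4 lets TAU participants move to psilocybin after the six-month follow-up, once the safety committee is satisfied on safety and preliminary efficacy.

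**The concern.** The trial has one primary endpoint, and its window decides what the between-arm comparison measures. Two features of the literal 12-month window work against a psilocybin-versus-TAU reading.

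1. The switch falls inside the window. In a comparison by randomised arm, an adverse event that follows a control's psilocybin dosing would count as a TAU event, unless a rule says otherwise. The protocol has no such rule.
2. The start is defined by Dosing 1. A TAU participant has no such date, or has one only after switching. Read literally, TAU events are either not collected until a switch or are collected from a date left to local choice.

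Apart from the switch, a yes/no count over a year fills up with background events in both arms, so an excess around dosing is harder to see. Section 9.1 makes any inpatient admission an SAE, and the population is prone to relapse. In an open-label trial whose stated purpose is safety, the window should be fixed before data are seen, and it should not be one that pulls the contrast towards no difference.

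**Working it through.** **No plan figure to reproduce.** Section 10.4 states that 40 participants (20 per group) were chosen for feasibility without a power calculation, and no AE rate is given. The check therefore sets the passages side by side and then illustrates the size on assumed rates.

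**Step 1: the windows.**

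| Source | Window implied | Covers switched controls? |
|---|---|---|
| 4.3 with 5.2, 5.4, 9.3, 11.2 | Dosing 1 to week 52 | Yes, from six months on |
| 5.2 visit title, 4.4, 8.2 | to week 9 | No |
| 15 | to six months | No, excluded in words |
| 10.2 (the analysis) | none stated | not addressed |

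Sections 5.4 and 15 also disagree on when the study is complete.

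**Step 2: power on simple assumed proportions.** Two-sided Fisher test at 0.05, 20 v 20. Power is the sum of binomial probabilities over all tables with p < 0.05.

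| Assumed any-AE risk (psilocybin v TAU) | RR | Power |
|---|---|---|
| Week 9: 80% v 40% | 2.00 | 65% |
| Week 9: 90% v 50% | 1.80 | 74% |
| Week 9: 70% v 30% | 2.33 | 60% |
| Month 12: 95% v 80% | 1.19 | 17% |
| Month 12: 90% v 70% | 1.29 | 24% |
| Month 12: 95% v 90% | 1.06 | 2% |

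**Step 3: one model carried through all windows.** Assume a constant background AE hazard λ in both arms and an acute AE probability q from psilocybin dosing. With w weeks of follow-up:

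- TAU risk = 1 − exp(−λw)
- Psilocybin risk = 1 − (1 − q)·exp(−λw)
- Risk in switched controls = 1 − (1 − q)·(1 − TAU risk)

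Take a TAU risk of 0.30 by week 9 and q = 0.80. Weeks 1 to 9 are 8 weeks, so λ = −ln(0.70)/8 = 0.0446 per week. Week 24 gives w = 23 and week 52 gives w = 51.

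| Window | Psilocybin | TAU arm | RR | Power |
|---|---|---|---|---|
| Week 9 | 0.86 | 0.30 | 2.87 | 0.94 |
| Six months | 0.93 | 0.64 | 1.45 | 0.50 |
| 12 months, no switch | 0.98 | 0.90 | 1.09 | 0.03 |
| 12 months, all controls switch | 0.98 | 0.98 | 1.00 | no difference left |

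With TAU week-9 risk varied over 0.15 to 0.45 and q over 0.6 to 0.8, the RR ranges are 1.73–5.53 at week 9, 1.13–2.34 at six months and 1.01–1.44 at 12 months without any switch.

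**Step 4: SAEs.** Assume a 52-week TAU risk of 0.50, an acute SAE risk of 0.05 to 0.10, and a hazard ratio for hospitalisation of 0.5 to 1.0. The RR is 0.98–1.89 at week 9 and 0.66–1.10 at 12 months without a switch. Power is at most 0.12 in any window.

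**The case against.** The strongest reply is that the protocol does give one window. Sections 4.3, 5.2, 5.4, 9.3 and 11.2 all lead to 12 months, and no passage restricts AE/SAE incidence to week 9 or to month six. The week-9 title is a visit label, used mainly to time secondary scales, fMRI, BDNF and laboratory tests. The six-month statement concerns when results are posted. This is right. A reader might infer that no primary contrast exists at all, or that AE and SAE at three windows make six rival primary analyses. The documents do not support either reading.

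A reader might also infer that the windows could give opposite safety conclusions. They do not support that either. In every any-AE scenario above the RR falls towards 1 and does not cross it. Only the SAE point estimate can change direction. That requires an assumed benefit on hospitalisation, and no SAE comparison in these scenarios has useful power.

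It can further be said that this is a pilot: section 5.1 admits limited power, section 10.2 puts descriptive frequencies first and records event dates and relatedness, section 10.1 focuses safety analysis on the dosed cohort, and section 9.5 provides committee reviews. An acute excess would be visible in those listings. That lowers the risk of harm going unseen, but it does not repair the planned between-group comparison.

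An analysis cut-off may be left to an SAP, which is not at hand. The inconsistent labels, the completion dates in 5.4 and 15, and a collection start that one arm does not have are statements in the protocol itself.

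**Conclusion.** The point holds. The primary time frame is labelled inconsistently. The window that follows from the wording of 4.3 mixes TAU with psilocybin exposure after six months, if controls switch, and has no defined start for TAU. Followed literally, the between-arm comparison is pulled towards no difference.

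The existence of the problem rests on the text alone. Its size rests on assumption: no AE rates are given, switch uptake is unknown, and the switch depends on the safety committee. The relapse figure in section 2 (more than 50% among those who recover) has no time frame and supports only the plausibility of frequent background events. Within the assumed ranges, a week-9 any-AE excess with RR 1.73–5.53 shrinks to 1.01–1.44 at 12 months from background events alone, and to 1.00 if all controls switch.

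**What to change.** In sections 4.3 and 10.2:

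- State one cut-off for the primary between-arm AE/SAE contrast that precedes the control switch. Week 9 already carries the label. The six-month visit, before any switch, would also be valid.
- Start the window at a matched point in both arms, such as randomisation or baseline, with the corresponding week for TAU in place of Dosing 1. Align sections 8.2, 9.3 and 11.2.
- Report AE/SAE incidence to 12 months as secondary, both as proportions and as events per participant-month. Show post-switch events in controls separately and do not count them as TAU events.

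Reconcile section 5.4 with section 15 on completion of the study. Rename the week-9 visit if it is not the primary time point.

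The cost is mainly wording and analysis, since the safety visits are already scheduled. If the start is set at randomisation or baseline, AE recording begins slightly earlier than Dosing 1. The downside is that events after the cut-off leave the primary contrast, but they are still fully reported.
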